### 9.2 Cost Data Collection

Cost data to be collected are of two types: 1.Recurrent costs and 2.Capital costs – i.e. those only incurred once. The first kind of data will be recorded on each day in the field. The second type of costs data will be recorded aggregately for the study and allocated to each community according to its relative population. Details on filling out these forms are described in section 10.8

The cost data collection will be done by filling out the following five forms. These forms can be found in Appendix 1:

- Form 0: Capital Costs
- Form 1: Medical Personnel Costs
- Form 2: Non-Medical Personnel Costs
- Form 3: Field Consumables’ Costs
- Form 4: Lab Costs

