At the end of the day of mass treatment in all grappes, health workers will tally the number of individuals recorded on the census who have been treated. For those grappes assigned to the standard coverage arm, if 80% coverage has been achieved, no additional treatment days will be necessary. If 80% coverage has not been reached, one extra day will be scheduled and health workers will inform village chiefs and community members of the date of their return. After two visits, mass treatment will conclude for that community, regardless of the attained coverage. In the case of over or under treatment for that round, the community will still be analyzed on an "intent to treat" basis as described in Chapter 16, data analyses plan.

For those grappes assigned to the enhanced (>90% or more) coverage arm, up to three additional treatment days (for a total of four days) can be scheduled. Before returning for each follow-up day, health workers will compile a list of all individuals recorded on the census who did not yet receive mass treatment. Village leaders and trachoma volunteers will be given this updated list and asked to identify and mobilize those who missed treatment, informing them of the date of the return visit and encouraging their participation in follow-up visits. After four visits, mass treatment will conclude for that community, regardless of the attained coverage.

All those who present for treatment will be treated. This is true even in communities randomized to standard treatment, meaning that coverage could be as high or higher in communities randomized to standard treatment as those assigned to enhanced coverage.

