### 9.1 Overview

The cost effectiveness analysis will be based on community cost estimates that we will calculate using the cost collection instruments described below. For each community, we will collect cost information regarding: all medical and non-medical personnel involved in the study and all consumables used. We will also include laboratory costs attributable to screening/treating each community. The totality of the equipment costs - such as vehicles and field equipment costs – and laboratory costs will be recorded aggregately and then allocated to each community according to the community population.

The cost collection *per se* will be organized as follows:

For each field trip/intervention, a designated member of the team will fill out the recurrent costs forms. Equally, this designated member of the team will be in charge of filling out the capital costs that are only incurred once for resources shared across different communities.

The filled forms will be double entered using the data entry software “Access” by two different data entry clerks. The double-entered data will be verified, and any differences in data entry will be checked against the paper forms. The verified dataset will be sent to our health economist [name] who will analyze the data.

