## 10.8 Cost Forms

### *Form 0: Capital Costs*

This form contains cost information on any vehicle used during the study and field costs incurred only once. This table will be filled out only once and not for every field trip. Capital costs will be imputed to each village on a population based proportional basis at the end of the study.

The table referring to capital costs for vehicles:

1. Average petrol cost per kilometer/miles: Record the cost of petrol, in the currency of the country, at the beginning and end of the field trial. Add these 2 values together and divide by 2 to get the average cost. Conversions into US\$ will be performed at the end of the study.
2. State whether the car was bought or rented
3. State the purchase price, in the currency of the country, when applicable.
4. State the daily cost, in the currency of the country, of the vehicle if it is rented
5. State the years of useful life attributable to the car. This will be calculated based on the year of make of the car and the number of kilometers ran by the car.

6. State the resale value of the vehicle (if it is not resold at the end of the study, state what the likely resale value would be).

The table referring to field equipment capital costs:

For each item of equipment:

1. The number of units
2. The price/unit in the currency of the country
3. State whether the good was donated or purchased
4. If the good is donated, state what its market value would be.

*Form 1: Medical Personnel Costs*

Form 1 will be filled out for every day in the field.

At the top of the form:

1. The date of fieldwork will be recorded in the format: “1st January 2008” (to avoid American MMDDYY versus British DDMMYY formatting).
2. The location(s) of fieldwork (the name of the community/communities worked in)
3. The activity/activities performed that day (e.g. sensitization, census, examination, treatment)
4. State clearly the number of people covered by the activity e.g. “100 children examined”, “150 people treated”.
5. The distance traveled (state Km or miles) that day by each vehicle separately

Medical personnel table:

1. The position of the medical personnel involved (e.g., ophthalmic nurses). Each person is written on a separate row
2. The number of hours spent working that day (including travel to and from location from accommodation)
3. The tasks performed that day by that person

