#### 16.2.1.1 FREQUENCY: 1. SIX MONTHLY VERSUS YEARLY; 2. YEARLY VERSUS STOPPING RULE

To compare the Trachoma control intervention with a 6 months frequency to that of 12 months frequency (in Niger) we will first of all calculate the average cost per community (adding those recurrent costs to those prorated capital costs and the laboratory costs) in the 6 months arm. We will do the same for those communities in the 12 months arm. Then, we will apply an

incremental cost effectiveness analysis approach and we will calculate the ratio resulting from dividing the differences in average cost of those two modalities of intervention by the difference in their average effectiveness.

To compare the yearly screening versus the stopping rule interventions in Tanzania and The Gambia, we will do similarly and calculate the average cost and average effectiveness of those communities in each arm. Then, we will calculate the incremental cost effectiveness ratio by dividing the cost differential by the effectiveness differential.

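### Vehicle purchase and field-equipment costs are shared by population, so the extra use caused by more rounds or treatment days largely drops out of the cost-effectiveness ratios; the handling of daily vehicle rental is inconsistent

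*Protocol*

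**What the plan says.** The allocation rule appears three times in the Protocol.

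- Section 9.1: the total of equipment costs, including vehicles and field equipment, "will be recorded aggregately and then allocated to each community according to the community population". The same sentence covers laboratory costs, which this point does not address.
- Section 9.2, on capital costs: "The second type of costs data will be recorded aggregately for the study and allocated to each community according to its relative population".
- Section 10.8, Form 0: "Capital costs will be imputed to each village on a population based proportional basis at the end of the study".

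Section 16.2.1.1 builds the average cost per community by "adding those recurrent costs to those prorated capital costs and the laboratory costs" and divides the difference in average cost by the difference in effectiveness. Section 16.2.1.2 does the same for coverage.

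Section 9.2 describes capital costs as those incurred only once. Form 0, which is completed once, nevertheless has the instruction "State the daily cost, in the currency of the country, of the vehicle if it is rented". It also takes a petrol cost per unit of distance, and it bases a vehicle's useful life partly on kilometres run.

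Cost Forms 1–3 are completed for every field day. They record date, location, activity and "The distance traveled (state Km or miles) that day by each vehicle separately". Vehicle repairs are entered on Form 3.

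**The concern.** Field activity differs between arms by design. Table 1 sets 3 annual against 6 biannual rounds in Niger. Under section 8.2 a Niger community on standard coverage gets at most two treatment days per round, whereas on enhanced coverage "up to three additional treatment days (for a total of four days) can be scheduled". Section 8.4 gives one day against two in The Gambia. Stopped communities in Tanzania and The Gambia have fewer rounds (section 8.6).

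A population key ignores all of this: two communities of equal size carry the same vehicle and equipment charge whatever their arm. Section 1.2 names extra distribution days as part of the enhanced effort, and section 1.3 says the added cost of six-monthly treatment or higher coverage must be weighed against its benefit. The rule removes part of that added cost from the numerator. The direction is predictable: biannual treatment and enhanced coverage look cheaper than they are, and stopping looks less cost-saving.

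**Working it through.** The Protocol gives no cost figure, so there is nothing to reproduce. The check applies the stated rule algebraically and then compares it with shares of use.

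**1. What the rule does.** Let K be the shared pool, n_j the population of community j, N the total population, and m the number of communities in each arm being compared.

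- Charge to community j = K × n_j / N.
- Difference in average charge = K × (N_A − N_B) / (N × m).

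Rounds, days and distance do not appear. If N_A = N_B the difference is zero. If the populations differ, it reflects headcount and not use.

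**2. Inputs for use.**

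- Niger rounds: 3 v 6 (Table 1). Maximum days per round: 2 v 4 (section 8.2).
- The Gambia days per round: 1 v 2 (section 8.4), over 3 annual rounds.
- Stopping arm: 40% to 80% of communities stop after one or two rounds (section 4.4.1).
- Surveys: 7 (baseline and months 6 to 36) with 2 days set aside for each (sections 7.1 and 7.5), so 14 survey days per community in every arm.
- Assumptions: equal arm populations, and one unit of vehicle and equipment use per field day.

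**3. Niger, maximum treatment days per community over three years.**

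| Cell | Treatment days | With 14 survey days |
|---|---|---|
| Annual, standard | 3 × 2 = 6 | 20 |
| Annual, enhanced | 3 × 4 = 12 | 26 |
| Biannual, standard | 6 × 2 = 12 | 26 |
| Biannual, enhanced | 6 × 4 = 24 | 38 |
| Sum | 54 | 110 |

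Annual v biannual:

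- Treatment only: (6 + 12) : (12 + 24) = 18 : 36, or 33:67.
- With surveys: (20 + 26) : (26 + 38) = 46 : 64, or 42:58.
- With surveys but one treatment day per round: (14 + 3) : (14 + 6) = 17 : 20, or 46:54.

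**4. The Gambia, coverage (annual arms).**

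- Treatment only: 3 × 1 : 3 × 2 = 3 : 6, or 33:67.
- With surveys: 17 : 20, or 46:54.

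**5. Stopping v annual.** If a fraction s of communities stops, mean rounds are 3 − 2s (stopping after one round) or 3 − s (after two). For s from 0.4 to 0.8 these run from 2.2 to 1.4, and from 2.6 to 2.2.

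- Stopping arm's share of treatment rounds: lowest 1.4 / (1.4 + 3) = 32%, highest 2.6 / (2.6 + 3) = 46%.
- With 14 survey days and one day per round: 15.4 / (15.4 + 17) = 47.5% to 16.6 / (16.6 + 17) = 49.4%.

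**6. Part of the pool left out of the cost difference** (share of one arm minus share of the other; by population it is 0).

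| Comparison | Pool serves treatment only | Pool also serves 14 survey days |
|---|---|---|
| Niger frequency, maximum days | 33% | (64 − 46) / 110 = 16% |
| The Gambia coverage | 33% | (20 − 17) / 37 = 8% |
| Stopping v annual | 7% to 36% | 1% to 5% |

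**The case against.** Much of the opposing case stands, and it narrows the point.

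- **Not all vehicle cost is affected.** A reader might infer that the ratios miss vehicle cost altogether. They do not. Repairs are recorded daily, and a petrol rate per unit of distance beside recorded daily distance points to fuel charged by use. Personnel hours, per diems and consumables are also daily, so much of the enhanced effort is captured. What remains is vehicle purchase (depreciation), field equipment and possibly rental.
- **Rental is not settled.** A reader might infer that rental is certainly shared by population because it is on Form 0. But Form 0 asks for a unit rate, which becomes a cost only when multiplied by days, and the once-only definition in section 9.2 does not fit rental. The text is inconsistent, and the passages must be reconciled.
- **The cancellation is exact only for equal populations.** Niger communities alone range from 250 to 600 people, so arm totals can differ.
- **The larger shares are upper-end illustrations.** They use maximum days, and the treatment-only figures leave out the surveys common to all arms. Distributors based locally may need less than one vehicle-day per treatment day.
- **Sharing fixed cost by headcount is a known convention.** A vehicle bought once may cost the same whatever the number of rounds.

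The last argument does not remove the concern. The Protocol itself ties useful life to kilometres run, and it wants the cost of extra effort weighed between arms. A key that ignores effort works against that purpose, and the distortion has a known direction.

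**Conclusion.** The point holds for vehicle depreciation and field equipment. Under the stated rule, and with arms of similar total population, this pool adds about zero to the cost difference although its use for treatment follows the randomised factors. The added cost of biannual treatment and enhanced coverage is understated, and so is the saving from stopping. For daily rental the finding is an inconsistency between section 9.2 and Form 0.

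Total study cost is not lost; its attribution to arms is. Depending on how far the pool also serves surveys, and on the days actually used, about 8% to 33% of the pool is missing from the increment for Niger frequency or The Gambia coverage, and about 1% to 36% for the stopping rule. These are shares of an unknown pool. It would be wrong to read 33:67 as the bias in a ratio, because without cost figures the money effect cannot be stated and may be small beside personnel and consumables.

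The primary trachoma and infection comparisons are untouched. Section 1.1 nevertheless lists cost-effectiveness as one of two major activities, so the rule should be changed.

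**What to change.** Amend sections 9.1, 9.2, 10.8 and 16.2.1 as follows.

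1. Allocate vehicle depreciation and rental by vehicle-days or kilometres, and field equipment by field days, using the date, location, activity and distance on cost Forms 1–3.
2. State how a day that covers several communities or activities is split.
3. State that rental and fuel are recurrent costs: daily rate × days, and petrol rate × distance. Form 0 can keep the rates.
4. In the programme-perspective ratio, separate treatment days from research survey days, and say how the surveys that feed the stopping decision are classed.
5. Keep population allocation as a sensitivity analysis.

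The cost is modest extra analysis and a small clarification of the forms. The main inputs are already collected each field day.

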## Chapter 10: Study Instruments

---

### 10.1 Overview

The data to be collected for this study consists of household information, and clinical and laboratory information on the child. In addition, data are collected on the mass treatment intervention, and details of the study process. In the next section, we describe the forms that are used to collect these data. These forms can be found in Appendix 1.

### 10.2 Census Forms

Overview: The baseline census form is used to collect information on each household in the communities randomized to this trial. It is the central document that provides information for the following:

- Selection of households with eligible children in the community
- Selection of children within a household when there is more than one eligible child
- Master List for Surveys
- Data base for mass treatment
- Environmental factors at the household level that may be important for trachoma

Description of how the census is to be conducted, and appropriate numbering of doorways is described in Chapter 6 for this study. A household is defined in Tanzania as a unique doorway belonging to a family. In Niger, a household is a family unit with one male head of household and often more than one wife (up to four wives), sleeping regularly in the same compound. In The Gambia, a household is a group of people who eat from a single cooking pot. The definition of resident in the household means a person who has slept in this household for at least three month in the past (or if age less than 3 months, was born not the household) or who intends to reside with the family for the next six months. In this section, details are provided on filling in the Baseline and Update Census forms. This section should be used with the forms in Appendix One (Study Forms).

#### 10.2.1 Baseline Census Form (Form 1)

Identification numbers:

GRAPPE/EA/VILLAGE\_\_ \_\_

In Niger, use the first two numeric digit entries to identify the grappe; In The Gambia, use the entry to identify the Enumeration Area; for Tanzania, use the entry to identify the village.

VILLAGE/MTAA: \_\_ \_\_

In Niger and The Gambia, use the second numeric two digit entry code to identify the village; in Tanzania, use the entry to identify the mtaa.

HOUSEHOLD NUMBER: \_\_ \_\_ \_\_

Use this three digit alphanumeric entry to uniquely identify a household; this number is also written on the door of the household.

Village Name: write in the name of the village

Name of head of Household: Write in the name of the head of the household. This may be provided by the neighborhood leader or another neighbor if the head or another adult in the family is not home.

Census taker: insert the initials of the census taker for this household. Each census taker should have a unique set of initials, including a number if there is more than one person with the same initials.

Date: insert the date in which the household census was completed (or the date at which census gathering had to be stopped and no information was provided). Use DD/MM/YY format.

1. Is there an adult home to answer questions?

If yes, mark “yes”. If not, the census taker should determine when would be a better time to return to get the information. If the family is traveling and not returning during the time of the census, then the census taker must indicate the reason for being unable to census. If there is not information on the family, s/he MUST return at least three times at different times over the course of the village census to try and catch an adult at home. If the census taker is unsuccessful, then mark “no” unable to census and provide a reason why. This household will not be chosen as a source of sentinel children, as detailed information will not be available on the children, but census information may be provided at the time of mass treatment, if the family returns for that activity.

2. How many years of education has the head of household completed?

Ask the question of the adult, and make sure that the answer is years completed, not including starting but not completed. Write in the number of years. If the answer is a grade, translate that into years completed. For example, in Tanzania the answer maybe Form one, in which case eight years of education has been completed. If the adult does not know, write letter “X for unknown.

3. How far away is the nearest water source?

We will measure the distance to water by asking how long it takes to walk one way directly to the nearest source of water. Time will be measured relative to the time it takes to do common tasks, such as boil water, cook ugali, or other tasks. Once the persons can provide an estimate, code as either less than 30 minutes, 30 minutes to one hour, or more than one hour. Each country will have its own code of relevant tasks that estimate time.

4. Has there been a health education program to promote face washing in this village in the last year? I do not mean a radio campaign but a local program in your village.

This is an optional question for areas in which the full SAFE strategy has been implemented. It helps determine if the health education campaigns have reached the village level.

5. OBSERVE: Does this household have a latrine:

The census taker will look in the compound or area around the house for a latrine. If one is not visible, the census taker will ask the interviewee if the household has a latrine. If yes, the team member will ask to see it. If it is within 60 feet (20m) of the house, it will be counted as a latrine for that household.

6. OBSERVE: Is the doorway area clear of garbage or waste?

The census taker observes the cleanliness around the doorway of the house. S/he will be standardized to observe the area around the doorway for evidence on the ground of leftover food or animal or human waste. Waste water or plant detritus does not count as waste. If there is a large animal pen within 25 feet (about 8 m) of the doorway, this will be recorded and counted as unclean doorway.

7. Household List: note that to the left of each name slot is a pre-printed number in sequential order. This two digit code is the unique person code for each person in the household. Use it when needed to identify the mothers of children as described below.

Name: List the names of all persons who reside in this household, as defined above. Start with the head of household. List the first name, last name, and an optional place for alias if needed.

Sex: Note the sex of the person as “M” for male and “F” for female.

Date of Birth: If it is possible to obtain a date of birth, record the date of birth: use DD/MM/YY format. If only the year is known, fill in “x” for the unknown numbers. Use a vaccination card or MCH card if available to get the birthdate of children, and a voting card or other piece of ID for the adults if available. If the entire date is unknown, then skip to the column labeled “age”

Age: use this column if no birthdate, or at least year of birth, can be obtained. Use an events calendar specific for each region to estimate the age of the person. If necessary, have other family members assist in determining the age. Avoid having a consensus using round numbers or last digits with 5's as it indicates digit preference; try to get the person and/or family members to be as precise as possible. For children age less than ten, indicate years and months if possible. For children less than age one year, insert a zero for years.

**Mom:** For each child age less than ten years, insert the two digit person code for the primary caretaker of the child. This will help identify the child in subsequent surveys.

**Child Face status:** The census taker will make observations on the cleanliness status of each child ages five years and under who are present at the time of the census. S/he will be standardized to measure a clean face as the absence of ocular discharge or “sleep” on the eyelashes or lids, the absence of nasal discharge on the nares and cheeks and lips, and the absence of flies on the face when observed for 3 seconds. The presence of any one sign is evidence of an unclean face. If the child is not present or cannot be observed, indicate “X” for each sign as “don’t know”. Otherwise, record yes or no for presence of sign on the child’s face.

**Random number:** an optional column for study sites where the data entry cannot be completed prior to selecting an eligible child in a household, and a random number assignment is made in the field. In the field, the census takers will have a Table of random numbers with a random start. They will then go horizontally across the page as they assign each child, starting with the first closest to the top, a random number in order that they appear on the table. As the number is assigned, it is crossed off the table. The child with the lowest number is the one selected from that household. For example, if child 04 has number 54 and child 05 has number 16, child 05 is the selected child. Note that if child 05 is not available for the survey, another household entirely is selected, not another child from the same household. This avoids always selecting younger children as they tend to be around the house.

